### Randomization

#### Camera use.

The study randomizes at the level of inspector shifts. Each inspector is assigned to wear a camera during a randomly selected 50% of their shifts over the study period (treatment) and to work without a camera during the remaining shifts (control). Four hours before each shift, participants receive an automated text message indicating whether they must wear a camera for that shift. If a shift starts before 12 pm, the text message is sent the evening before at 8 pm to avoid contacting participants between 8 pm and 8 am. The treatment message is sent within a time span that allows participants to have time to bring the camera to work while minimizing the risk that participants select routes based on whether they carry the camera or not (as some inspectors have freedom in choosing routes). While this design informs inspectors about their condition assignment in a timely manner, it does not eliminate the risk that inspectors adjust their inspection style and manner of coping with passenger conflicts in anticipation of their assigned condition. To assess this bias, we will examine whether outcomes vary across different notification times, on the assumption that shorter notice leaves less room for anticipatory adjustments.

The block-randomization design guarantees an even 50/50 split between treatment and control shifts for every participating inspector. Compared to the field trial by Ariel and colleagues [4], this approach offers key advantages: it ensures treatment and control observations are independent of inspector- or shift-specific characteristics, removes clustering by inspector, increases statistical power, and makes it more likely that randomization produces genuine *ceteris paribus* conditions [31,32]. Despite these strengths, this design carries a risk of contamination, as the same inspectors alternate between treatment and control shifts and may carry learned behaviors, fatigue effects, or other carry-over biases from one condition to the other [see, e.g., 33].

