#### Team-level.

Inspectors from Company 1 occasionally and Company 3 always work in pairs, potentially causing spillover effects from the expected benefits of wearing a camera to colleagues. This is accounted for in the survey by asking whether the inspector worked alone or together with a colleague during the shift. For inspectors from the subcompany hired by Company 3 who always work with two or three colleagues, the randomization and treatment are allocated at the dyad-team-level to prevent spillover effects.

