#### Shift survey.

At the end of each shift, inspectors receive an automated text message prompting them to complete a short questionnaire. This survey captures self-reported experiences of victimization (ranging from verbal condescension to physical aggression and violence), perceived safety, whether they worked with a colleague, and whether they wore a camera. The latter information enables estimation of the local average treatment effect among inspectors who comply with their randomly assigned treatment, using instrumental variable regression [34]. In the remainder of the paper, we refer to this questionnaire as “the survey.”

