#### Moderators.

We include a variety of moderators to explore heterogeneities in the camera’s effect on victimization. One group of moderators is measured in the initial baseline survey and includes the inspector’s gender, age, ethnicity, household status, work experience in the company, BMI, prior victimization, prior sick leave due to victimization, baseline sense of safety, and attitudes toward cameras and management. Another group of moderators includes company, shift start and end time, whether the inspector worked alone or in units for some or most of the shift, camera placement on the uniform, and whether a colleague was wearing a camera. All of these moderators are pre-treatment variables and are voluntarily provided by participants.

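### Not all listed moderators are pre-treatment: camera placement has no control-arm value, and for the team-allocated Company 3 guards a colleague's camera repeats the inspector's own assignment

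*Protocol article*

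**What the plan says.** The Moderators subsection lists two groups. Of the first it says "One group of moderators is measured in the initial baseline survey"; these are personal characteristics, work history and attitudes. The second group is not tied to any baseline instrument. It contains company, "shift start and end time, whether the inspector worked alone or in units for some or most of the shift", and "camera placement on the uniform, and whether a colleague was wearing a camera". The subsection then covers both groups with one statement: "All of these moderators are pre-treatment variables and are voluntarily provided by participants".

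Four other places bear on that statement:

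- Camera use: "Four hours before each shift, participants receive an automated text message indicating whether they must wear a camera for that shift". For shifts starting before noon the message goes out at 8 pm the evening before.
- Shift survey: "At the end of each shift, inspectors receive an automated text message prompting them to complete a short questionnaire". Its items include "whether they worked with a colleague, and whether they wore a camera".
- Camera visibility: the control condition has neither camera nor badge.
- Team-level, for the Company 3 security subcompany: "the randomization and treatment are allocated at the dyad-team-level to prevent spillover effects".

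Data analyses plans to explore moderators with causal forests, targeting τ(X) = E[Y(1) − Y(0) | X = x].

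**The concern.** A CATE given X is a treatment effect only if X cannot be altered by the assignment and both arms occur at each value x. The blanket statement is the plan's only warrant that every listed moderator meets the first condition. If it is false for some of them, a forest that includes those variables may split on a stand-in for the treatment, or on something the treatment changed, and report the result as effect heterogeneity.

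The Objective asks under which conditions cameras prevent victimization, as well as whether they do. The moderator analysis is a main source for that second part, and its results could guide where cameras are deployed.

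**Working it through.** The plan gives no figure on this point, so there is none to reproduce. The check compares the timing and definition of each moderator with the assignment.

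**1. Classification**

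| Moderator | Fixed before the message? | Both arms present at each value? |
|---|---|---|
| Baseline-survey items | Yes | Yes |
| Company | Yes | Yes |
| Shift start time | Effectively yes; the message is timed from it | Yes |
| Shift end time | Only if rostered | Yes |
| Solo or team working | Only if rostered | Yes |
| Camera placement | No; exists only when a camera is worn | No |
| Colleague's camera, Company 3 guards | No; follows the team assignment | No, apart from non-compliance |
| Colleague's camera, Company 1 pairs | Not tied to own assignment by the documents | May be |

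**2. Camera placement.** Control shifts have no camera, so placement is undefined there. Among compliers, P(camera arm | any recorded placement) = 1. The only control shifts with a placement are those on which a camera was worn against assignment. They are a self-selected group and do not supply the missing Y(0).

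**3. Colleague's camera among the guards.** Intervention setting says that these guards always work in units of two to three and that their subcompany does not otherwise use cameras. With allocation by team, the members of a unit share one assignment. If the whole unit is in the trial and complies, colleague's camera = own assignment, and at a fixed value only one arm is observed. Size: 18 guards / about 60 inspectors = 0.30. This is an upper bound, because recruitment is voluntary, and it is a share of inspectors, not of shifts.

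**4. Staffing and end time.** Working with a colleague is collected after the shift. That alone does not make it a consequence of assignment. If it did depend on assignment, the bias can be illustrated under assumed inputs that are not in the protocol:

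- true effect zero for everyone, outcome SD 1, 1:1 assignment;
- a binary moderator M with P(M=1) = 0.5 under control and p = 0.5 + s under camera;
- a latent shift risk correlated 0.5 with the outcome and 0.5 with the normal variable that determines M.

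With c = Φ⁻¹(p), and φ(0)/0.5 = 0.798 for control, the spurious effects are

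- M=1: 0.5 × 0.5 × [φ(c)/p − 0.798]
- M=0: 0.5 × 0.5 × [0.798 − φ(c)/(1 − p)]

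| s | φ(c) | M=1 | M=0 |
|---|---|---|---|
| 0 | 0.399 | 0 | 0 |
| 0.1 | 0.386 | −0.038 | −0.042 |
| 0.2 | 0.348 | −0.075 | −0.090 |
| 0.3 | 0.280 | −0.112 | −0.150 |

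A simulation of 2,000,000 shifts agrees to within 0.004 (for example −0.110 and −0.153 at s = 0.3), and the overall intention-to-treat difference stays at 0. For scale, the plan's f² = 0.003 corresponds to d = 2√0.003 = 0.11 at 1:1 allocation. So strong dependence could produce false subgroup effects as large as the planned detectable effect, and no dependence produces none. The negative sign follows from the assumed correlations.

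**The case against.** The strongest reply is that little depends on this. The moderators enter only the third, exploratory stage. Data analyses labels that stage as exploratory and promises conservative interpretation. The same section describes X as pre-specified characteristics of the inspector, a phrase that does not naturally cover placement, a colleague's camera or shift times. They may never enter the forest.

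Part of this stands. The composition of X is ambiguous, and it should not be taken as settled that the forest will use these variables. But the Moderators subsection lists them as moderators of the camera effect, and the forest paragraph is introduced as the exploration of moderators, so the text does not exclude them. The exploratory label and cautious testing deal with multiplicity; they do not repair a missing contrast. Nor is this detail that could be left to an analysis plan, because the protocol makes a positive statement that is incorrect.

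A reader might infer that all the shift-level moderators are contaminated. The documents do not support that:

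- Staffing follows largely fixed rules: pairs after 8 pm or 10 pm in Company 1, always solo in Company 2, always units for the security guards, and always solo for Company 3's four local-train inspectors.
- The protocol does not say whether end time is actual or scheduled. The automated survey prompt at shift end suggests that scheduled times are held.
- The one behavioural route mentioned is that some inspectors can choose routes, which the message timing is meant to limit.
- In Company 1 pairs, nothing ties a colleague's camera to own assignment, and many colleagues there have cameras anyway. It may be a legitimate source of variation.

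The Shift survey description does not list placement, so how it is recorded is unknown. If it were an inspector's fixed habit noted before assignment, it could be a valid covariate, but the protocol does not say so.

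**Conclusion.** The concern holds in limited form. The statement that every moderator is pre-treatment is wrong for two listed variables: camera placement in all companies, and a colleague's camera among up to 18 of about 60 inspectors. Neither supports the stated CATE contrast. For solo or team working and end time, the claim is right or wrong depending on whether rostered values are used; bias there is possible and not shown.

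Two wider conclusions do not follow. The main result is not at risk, because the intention-to-treat and two-stage least squares models contain no moderators. The answer on conditions is not wrong as a whole, because the baseline-survey moderators, company and start time remain sound and the field observations address the same question.

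The verdict assumes that placement is recorded per shift, and that a guard's whole unit takes part and broadly complies. If a unit included a non-participant, that colleague would have no camera in either arm, but the value 'colleague has a camera' would still lack compliant control shifts. This is a should-fix confined to the exploratory heterogeneity stage.

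**What to change.** - Replace the blanket statement with one that says which moderators are fixed before the assignment message and which are not.
- State the forest's X explicitly: baseline-survey items, company, and start time, end time and staffing from the roster as it stood before the message.
- Report camera placement descriptively, within camera shifts only.
- Keep a colleague's camera out of X for the team-allocated guards. Elsewhere, analyse it as a spillover exposure, using the colleague's assignment or camera status where that varies independently of own assignment.
- Optionally, add a sensitivity analysis limited to shifts rostered solo. It would exclude every security guard and is not needed to correct the statement.

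The cost is a few sentences, access to roster data, and the loss of one or two exploratory moderators that could not have been interpreted as planned. No data and no power for the main analysis are lost.

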### Data analyses

Our data analysis plan proceeds in three stages to comprehensively evaluate the impact of body-worn cameras. We will estimate the causal effect for two primary continuous outcomes: victimization and perceived safety. First, we will estimate the Intention-to-Treat (ITT) effect, which is the effect of the random *assignment* to carry a camera, regardless of actual use. This analysis preserves the benefits of the initial randomization. We will use an Ordinary Least Squares (OLS) regression model for this purpose:

$$Y_{i}=\beta_{\text{0}}+\;\beta_{\text{1}}Z_{i}+\epsilon_{i}$$

Here, Y_i is the outcome for inspector i, and Zi is a treatment indicator equal to 1 if the inspector was assigned to the camera group and 0 otherwise. The coefficient of interest, β1, represents the ITT effect.

Second, to account for potential non-compliance (i.e., inspectors not using their assigned cameras), we will estimate the Average Treatment Effect on the Treated (ATT). This represents the effect of actually using a camera for those who complied with the assignment. We will use the random assignment as an instrumental variable (IV) for reported camera use. The effect will be estimated using a Two-Stage Least Squares (2SLS) regression.

First Stage: Predict actual camera use based on the random assignment. Here, Di is an indicator for whether inspector i reported using the camera.

$$D_{i}=\gamma_{\text{0}}+\;\gamma_{\text{1}}Z_{i}+\nu_{i}$$

Second Stage: Use the predicted camera use from the first stage (D^i) to estimate the effect on the outcome. The coefficient δATT provides our estimate of the ATT.

$$Y_{i}=\lambda_{\text{0}}+\;\lambda_{\text{ATT}}{\hat{D}}_{i}+\eta_{i}$$

Finally, to explore potential moderators, we will investigate treatment effect heterogeneity. We will use causal forests, a machine-learning method designed to estimate Conditional Average Treatment Effects (CATEs), defined as τ(X)=E[Y(1)−Y(0)|X = x]. This non-parametric approach will allow us to flexibly explore how the treatment effect varies across a range of pre-specified inspector characteristics (X) without being constrained by linear interaction terms. These explorative subgroup analyses will be conducted and disseminated with careful consideration of sensitive moderator variables such as BMI and ethnicity. Further, we acknowledge that our exploratory subgroup analyses imply an increased false-positive rate due to multiple comparisons [38], which will be addressed by interpreting statistical significance tests conservatively and clearly labeling these results as’exploratory’ in the Results section.

For all OLS and 2SLS regression models, we will calculate cluster-robust standard errors to account for the statistical dependence between inspectors working in dyads. Furthermore, as a robustness check, we will re-estimate our primary models including inspector fixed effects to control for any unobserved, time-invariant characteristics of the individuals.

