The current study protocol outlines a randomized controlled trial of body-worn cameras that seeks to test whether wearing a camera on the uniform reduces victimization risk, using a design that advances the existing literature in several respects. We conduct a large-scale trial to help resolve the ongoing uncertainty over whether body-worn cameras have a robust effect at all. This test is conducted outside the U.S. policing context—specifically with Danish ticket inspectors—to help clarify the literature’s uncertainty regarding the context dependency of effects. Additionally, we incorporate a range of methodological strategies in our trial design that offer advantages over existing studies. Below, we review the current literature and its limitations and, on this basis, present the study protocol developed to address these gaps.

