### Measures

#### Outcome measures.

The primary outcome measure is victimization, ranging from verbal offenses and harassment to physical violence. In the survey, participants report whether they experienced each of the following passenger behaviors 0, 1, 2, 3 or more times during the shift: behaved unpleasantly toward the inspector; were rude or condescending; raised their voice or cursed at the inspector; filmed the inspector with their phone against their will; came uncomfortably close in a threatening manner; touched or grabbed the inspector in an unpleasant way; acted aggressively or threateningly toward the inspector (e.g., banging on the window or threatening with an object); made verbal threats; spat at the inspector; or used physical violence (e.g., pushed, hit, or threw an object at the inspector). We will use Mokken scale methods to combine these observed measures into a single victimization scale and assess its measurement quality.

The victimization survey instrument is developed based on previous research on passenger aggression [35,36] and on Company 1’s incident records, which document the specific behaviors that occur in the registered victimization events. By grounding our measure in these context-specific descriptions rather than in abstract theoretical categories or instruments developed for other settings, we enhance the construct validity of our victimization measure.

The secondary outcome measure is self-perceived safety, based on inspectors’ assessments of how safe they felt during their most recent shift. It is measured on a five-point Likert scale ranging from not at all (1), to a low extent (2), to some extent (3), to a high extent (4), and to a very high extent (5), using a set of questions evaluating the extent to which the inspector felt unsafe, feared being assaulted, and avoided a passenger for their own safety during the shift. These items will be combined into an additive scale.

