The primary and secondary outcome measures are based on inspectors’ subjective ratings of encountered passenger behavior and self-perceived safety during a shift. This reliance on self-report comes with the risk of expectancy bias, as inspectors may rate their experiences in accordance with treatment assignment—or conversely, may underreport benefits given some employees’ skepticism toward body-worn cameras. Blinding is not feasible, as inspectors are necessarily aware of whether they are wearing a camera—a common type of limitation in experimental social science research [37]. However, the parallel field observations provide some qualitative triangulation by offering independent insight into how staff-passenger encounters unfold.

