### Sample size and power analysis

The current study will sample approximately 3,000 shifts from up to 60 ticket inspectors employed by the three companies during a three to four months intervention period. As mentioned, our block-randomization design using work shifts, not individual inspectors, ensures that treatment and control observations are independent of inspector characteristics, effectively making the 3,000 shifts the sample unit [32].

Importantly, the sample size in the current study will provide very high statistical power to detect even small effects. A priori power analysis indicates that the planned sample size will yield 90% power to detect very small effect sizes (Cohen’s *f*^2^ = 0.003) in a regression model. Even under conservative assumptions of substantial attrition—such as 20% missing data due to loss of interest among inspectors who fail to complete the survey—the study is still expected to maintain 90% power to detect similarly small effects (Cohen’s *f*^2^ = 0.004).

Further data-structural and model-specification choices may reduce this power. For example, this could result from the use of cluster-robust standard errors to account for inspectors working in dyads, the imbalance in the number of observations across experimental conditions, or other anomalies that may arise during data collection. Nevertheless, given that our power calculations indicate the ability to detect even very small effects, it is unlikely that such factors will meaningfully compromise the overall capacity of the analyses to detect effects of a small magnitude.

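### Perceived safety is the secondary outcome under Outcome measures but one of two primary outcomes under Data analyses, so the protocol does not fix which result decides the trial

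*Protocol article*

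**What the plan says.** Three parts of the protocol article point to victimization as the single primary outcome.

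- Introduction: the trial "seeks to test whether wearing a camera on the uniform reduces victimization risk".
- Outcome measures: "The primary outcome measure is victimization, ranging from verbal offenses and harassment to physical violence". Safety is then ranked below it: "The secondary outcome measure is self-perceived safety".
- Outcome measures, in the paragraph on self-report, keeps the same ranking: "The primary and secondary outcome measures are based on" inspectors' own ratings.

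The section that governs the analysis ranks them differently. Data analyses opens its modelling plan with: "We will estimate the causal effect for two primary continuous outcomes: victimization and perceived safety". The same section later promises a fixed-effects robustness check on the primary models, without saying whether those cover one outcome or both.

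Multiplicity is mentioned once, for the causal-forest work: "our exploratory subgroup analyses imply an increased false-positive rate due to multiple comparisons". The power section gives one generic calculation that names neither outcome, no significance level and no sidedness.

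**The concern.** Perceived safety cannot be both the secondary outcome and one of two primary outcomes. All the sentences are current text, so this is not a superseded wording.

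The label matters because the abstract ties confirmation of the preventive hypothesis to practical consequences for deploying cameras. The protocol should therefore settle, before data are seen, which result confirms it. Suppose victimization shows no difference and perceived safety improves. Under Outcome measures, the trial has missed its only primary outcome. Under Data analyses, it has succeeded on one of two. Both reports could cite the protocol, and the choice between them could be made after the results are known.

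**Working it through.** **1. The rankings side by side**

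| Place in the protocol article | Victimization | Perceived safety |
|---|---|---|
| Introduction | object of the test | not part of the stated test |
| Outcome measures | primary | secondary |
| Data analyses | primary | primary |

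Data analyses is the only place that calls safety primary.

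**2. The plan's own power figure**

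Inputs, from Sample size and power analysis: "The current study will sample approximately 3,000 shifts from up to 60 ticket inspectors"; "A priori power analysis indicates that the planned sample size will yield 90% power to detect very small effect sizes", with f² = 0.003; and 20% missing data, which leaves 0.8 × 3,000 = 2,400 shifts, with f² = 0.004. Like the plan, this check treats shifts as independent. The significance level is my assumption (0.05), and I tried both one-sided and two-sided tests.

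Method: power for one regression coefficient, with noncentrality λ = f² × N (noncentral F for two-sided, noncentral t for one-sided).

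- N = 3,000, f² = 0.003: λ = 9.0. Power is 91.2% one-sided and 85.1% two-sided.
- N = 2,400, f² = 0.004: λ = 9.6. Power is 92.7% one-sided and 87.2% two-sided.
- The f² detectable with 90% power is 0.0029 and 0.0036 one-sided, which round to the stated 0.003 and 0.004. Two-sided it is 0.0035 and 0.0044, which give the stated pair only if the third decimal is cut rather than rounded.

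So the stated figure is reproduced, within 2 percentage points, by a single one-sided 5% test. No allowance for a second primary outcome is visible in it.

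**3. Error rate if both outcomes are primary and neither is adjusted**

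Assumed: each outcome tested at 5%, no true effect on either, and correlation ρ between the two test statistics (not given in the article).

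- Independent: 1 − (1 − 0.05)² = 0.0975.
- Correlated, two-sided: 1 − P(|Z₁| ≤ 1.96 and |Z₂| ≤ 1.96), with (Z₁, Z₂) bivariate normal. The one-sided version uses 1.645 in one direction.

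| ρ | Two-sided 5% each | One-sided 5% each |
|---|---|---|
| 0 | 9.75% | 9.75% |
| 0.3 | 9.5% | 9.3% |
| 0.5 | 9.1% | 8.8% |
| 0.7 | 8.3% | 8.0% |
| 0.9 | 7.0% | 6.8% |

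The two-sided column counts false results in either direction. Counting only false favourable results under two-sided 5% tests, the independent case is 1 − 0.975² = 4.94%, against 2.5% for one test.

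**4. What each reconciliation costs**

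- Victimization as sole primary: its test keeps the full significance level, and the power statement stands as written.
- Two primaries with Bonferroni at 0.025 each: family-wise error is 1 − 0.975² = 4.94% if independent and at most 5% otherwise. At N = 3,000 and f² = 0.003, power per outcome falls from 85.1% to 77.6% two-sided, or from 91.2% to 85.1% one-sided. The f² detectable with 90% power rises from 0.0035 to 0.0041 two-sided, or from 0.0029 to 0.0035 one-sided.

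**The case against.** The best defence is that the decisive outcome can be identified despite the stray label. The Introduction, Outcome measures and the Moderators section all centre on victimization, and the sentence in Data analyses says which outcomes are modelled, not what counts as success. That is fair, and it limits what may be concluded. It does not remove the conflict, because the outlying sentence is the one that introduces the analysis plan.

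Four stronger readings are tempting, and the article does not support them.

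- *Success on either outcome is enough to claim a preventive effect.* No sentence says so. Calling both outcomes primary leaves room for that reading, but the stated test concerns victimization.
- *The trial has no error control across its outcomes.* The article is silent on this, but a protocol article may leave significance level, testing order and outcome multiplicity to an analysis plan that is not shown. The silence is not a defect. The conflicting rank is, and a testing rule elsewhere would still leave the article giving two rankings.
- *Safety is the outcome more exposed to expectancy bias, so promoting it is especially risky.* Outcome measures applies expectancy bias to both outcomes, which come from the same unblinded shift survey, and the Discussion names victimization as the one that may be over- or underreported.
- *The error rate is nearly doubled.* That holds only near independence. Both scales come from one respondent about one shift, so the correlation may be substantial. Under two-sided tests the figure also includes false findings of harm.

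**Conclusion.** The concern holds as a contradiction in current text: perceived safety is secondary in one section and primary in another, which leaves open how a split result would be reported. The inflation from 5% to between about 7.0% and 9.75% is conditional. It applies only if both outcomes are treated as primary, each is tested unadjusted at an assumed two-sided 5%, and the correlation lies between 0.9 and 0. The article fixes none of these. The case for correction rests on the conflicting labels and not on that range. It is more than clerical, because the identity of the primary outcome determines what the trial may claim.

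**What to change.** Before analysis, reword the opening of Data analyses so that it names one primary outcome (victimization) and one secondary outcome (perceived safety). Add that the conclusion on a preventive effect rests on victimization, and say which outcome the primary models in the robustness check refer to. This takes a sentence or two, costs victimization no power, and leaves the power statement unchanged.

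Optionally, test safety confirmatorily only if victimization is significant. This holds the family-wise error of the pair at the nominal level at no cost to victimization. It is one legitimate choice among several and is not needed to resolve the contradiction.

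If two primary outcomes are really intended, change Outcome measures instead, state the adjustment, and restate the power. With Bonferroni the cost is the loss shown in the working: about 6 percentage points one-sided (91.2% to 85.1%) or 7.5 two-sided (85.1% to 77.6%) at f² = 0.003 and 3,000 shifts.

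### The primary ITT and 2SLS models omit shift timing and length, which the trial collects and calls pre-treatment, so some precision is given away; the estimate is not biased

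*Protocol article*

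**What the plan says.** Under Data analyses, the protocol article says of the ITT effect: "We will use an Ordinary Least Squares (OLS) regression model for this purpose". The printed equation regresses the outcome on assignment alone, and "The coefficient of interest, β1, represents the ITT effect". The two 2SLS equations contain no covariates either. The only planned re-estimation of the primary models adds inspector fixed effects as a robustness check.

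Under Outcome measures, "participants report whether they experienced each of the following passenger behaviors 0, 1, 2, 3 or more times during the shift", and "We will use Mokken scale methods to combine these observed measures into a single victimization scale". The analysed outcome is therefore a scale built from ten capped counts over the whole shift and treated as continuous. No exposure term is mentioned.

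Under Moderators, "Another group of moderators includes company, shift start and end time" among other shift-level variables, and "All of these moderators are pre-treatment variables and are voluntarily provided by participants". Their stated use is to explore heterogeneity. Under Camera use, the assignment message is timed from the start of the shift, so the start time must be known beforehand. Under Shift survey, an automated message goes out when the shift ends; the article does not say whether that end time is rostered or reported.

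**The concern.** An inspector who works longer, or at a busier or rougher time of day, has more opportunity to meet each listed behavior. The protocol itself hints that time of day matters: under Intervention setting, Company 1 inspectors on nationwide trains work in pairs late in the evening for safety reasons. Allocation is balanced 50/50 within inspector, and no stratification by shift time is described. Neither design nor model therefore removes this source of variance.

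Inspector fixed effects remove stable differences between people. They leave untouched the difference between one inspector's early and late shifts, or short and long ones.

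What is at stake is the width of the confidence interval in a trial that aims at very small effects and whose power section concedes that clustering and imbalance may erode power. Because the equations are printed, this is a stated choice and not a detail left to an unseen analysis plan.

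**Working it through.** **Inputs from the documents** (Sample size and power analysis): about 3,000 shifts; 90% power at f² = 0.003; after 20% missing data, 3,000 × 0.8 = 2,400 shifts and 90% power at f² = 0.004. Significance level and sidedness are not stated; 5% is assumed throughout.

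**Step 1: the plan's own figure.** F test with 1 numerator df, noncentrality λ = f² × N.

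- At 3,000 shifts, λ = 0.003 × 3,000 = 9. Power is 85.1% two-sided and 91.2% one-sided.
- At 2,400 shifts, λ = 0.004 × 2,400 = 9.6. Power is 87.2% two-sided and 92.7% one-sided.
- Smallest f² with 90% power, one-sided: 0.00286 and 0.00357, which round to the stated 0.003 and 0.004.
- Smallest f² with 90% power, two-sided: 0.00350 and 0.00438, which match the stated values only if cut off after one digit.

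The published figures are thus reproduced to their one-digit rounding with a one-sided 5% test.

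**Step 2: what adjustment buys.** If pre-shift covariates explain a share R² of the residual variance, then

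- SE ratio = √(1 − R²)
- equivalent shifts = 3,000 / (1 − R²)
- λ becomes 9 / (1 − R²)

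The documents give no R², so a range is assumed. Power is for a two-sided 5% test at unadjusted f² = 0.003 and 3,000 shifts.

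| R² (assumed) | SE ratio | Equivalent shifts | Extra shifts | Power |
|---|---|---|---|---|
| 0 | 1.000 | 3,000 | 0 | 85.1% |
| 1% | 0.995 | 3,030 | 30 | 85.4% |
| 5% | 0.975 | 3,158 | 158 | 86.8% |
| 10% | 0.949 | 3,333 | 333 | 88.5% |
| 15% | 0.922 | 3,529 | 529 | 90.2% |

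**Step 3: which R² is plausible.** An illustrative simulation, with every input assumed, used overdispersed counts averaging 0.5 to 4 events per shift, a coefficient of variation of shift length of 10% to 30%, and 35% evening shifts with a rate ratio of 1.5 to 3. Length and evening work explained 1.3% to 11.5% of outcome variance. That is worth 3,000/0.987 − 3,000 ≈ 40 to 3,000/0.885 − 3,000 ≈ 390 shifts, or a standard error smaller by about 1% to 6%. It modelled a raw count, not the capped Mokken scale, so it indicates the order of magnitude only.

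**Limits of the arithmetic.** It treats shifts as independent, as the plan's power statement does. Once inspector effects are in the model, the relevant R² is the share of the variance remaining within inspectors.

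**The case against.** The strongest reply is that nothing here is wrong. Unadjusted OLS on randomized shifts is valid and simple, and the benefit of adjusting rests on an R² that nobody has measured. That stands, and it is why the point is optional.

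A reader might infer that the effect estimate is biased because exposure time is ignored. The documents do not support this: assignment is random within inspector, so timing and length differ between conditions only by chance.

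A reader might also infer that the trial misses its stated 90% power unless it adjusts. That does not follow. The shortfall appears only under a two-sided 5% test, which the article does not specify; with a one-sided test the unadjusted power is already 91.2%. Even two-sided, adjustment reaches 90% only near R² = 15%, above the range in the simulation.

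Three narrower objections also hold in part. First, an advance start time is well supported, but a rostered end time is only inferred, and the moderators are provided voluntarily, so some values may be missing. Second, company is constant for an inspector, so it adds nothing once inspector effects are in the model. Third, the accumulation argument applies to victimization; for perceived safety, which Data analyses also treats as primary, it does not apply, and any gain would have to come from timing being prognostic in its own right.

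**Conclusion.** The point holds as a modest, avoidable loss of precision in the primary ITT and 2SLS analyses, and as nothing more. For an assumed R² between 1% and 15%, the standard error would fall by about 0.5% to 8%, equal to about 30 to 530 extra shifts. Power at f² = 0.003 would move from 85.1% to between 85.4% and 90.2% under an assumed two-sided 5% test. The lower and middle parts of that range look more likely than the top. The conclusion that adjustment is worthwhile does not depend on sidedness, because the proportional gain in standard error is the same either way. Priority is low.

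**What to change.** Before outcomes are analysed, pre-specify these covariates for the primary ITT model and for both 2SLS stages:

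- start-time band;
- planned shift length, provided a rostered end time is held before the assignment message is sent;
- inspector fixed effects, moved from the robustness check into the primary model. Inspector is the randomization block, and these effects absorb company. For the Company 3 guards, who are allocated by team, keep the planned dyad clustering of standard errors.

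Do not use end times reported after the shift, even though the article calls shift times pre-treatment: an incident can lengthen a shift, so a reported end time may be affected by the camera. If no rostered end time is held, adjust for start-time band and inspector only. Keep the unadjusted model as a sensitivity analysis, and state the significance level and sidedness next to the power figure.

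The cost is a short addition to the plan and a few dozen of about 3,000 degrees of freedom (at most 59 for 60 inspectors, plus a few for timing and length). Because allocation is balanced within inspector, this has a negligible effect on precision. Some shift times may be missing, so a rule for handling them should be fixed at the same time.
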